## Participants, interventions, and outcomes

### Study setting

This single-centre trial will be conducted at the Gansu Provincial Hospital, Lanzhou, People’s Republic of China. The hospital is a comprehensive top-ranked 3A facility integrating medical services with teaching, research, and preventive care. The facility was established in 1950 and is in the Northwestern part of China. The hospital currently has a total of 3370 beds across various medical and surgical specialties with outpatient facilities.

### Eligibility criteria

All burn survivors receiving burn care services at the study site will be screened for eligibility during the study period. Adult burn survivors aged ≥ 18 years with burn size ≥ 10% TBSA as assessed by the burn surgeon/burn care nurse (irrespective of the depth of the burn), absence of a confirmed psychiatry condition, renal failure, or diabetes mellitus and reachable on phone and WeChat will be considered for inclusion. Adult burn survivors who are unable to communicate or are enrolled in another rehabilitation trial will be excluded. Drop out will be ascertained based on participants exiting either the control or intervention before the 12th week with no intention to continue their participation. Participants for the follow-up process evaluation phase will be recruited from both arms of the trial. The intervention will be primarily provided and coordinated by two burn care nurses with referrals to other members of the multi-disciplinary burns team which comprises of burn surgeons, rehabilitation medicine specialist, and social worker/psychologist who are involved in caring for burn patients at the study site. These burn care nurses recruited to deliver the intervention will have at least 4 years working experience in the burn unit at the study site and must complete a mandatory training programme which covers contents of the comprehensive transitional care program for burn patients with theory and practice (18 h in total) and passed a competence test prior to participating in the study. Other nurses working in the same unit provide routine care to all patients and are not involved in the intervention. Since most of the nurses working in the unit are not involved with the intervention cases, the risk of contamination is minimal.

The objectives of the mandatory training programme were to enable the burn care nurses to be able to master the concept of transitional care; assess, manage, and monitor the transitional needs of burn patients using the Omaha System and make referral when applicable and demonstrate burns rehabilitation competencies (comprehensive scar, itch, and pain management; psychosocial care; aromatherapy; exercises and splinting; monitoring nutrition and hydration; and infection prevention). See Table 2 for details regarding the training programme.

**Table 2 Tab2:** Details of training programme for burn care nurses based on the TIDieR checklist

TIDieR checklist					
Why (goal/aim, rationale, and theory)	What (materials and procedures), when (schedule), how much (frequency, dose, and intensity of interventions), who (provider), and how (mode of delivery)	Where (location of the intervention)	Tailoring (personalized, titrated or adapted for individual circumstances)	Modifications (changes that occurred during study)	How well (intervention adherence)
The objectives of the mandatory training programme were to enable the burn care nurses to be able to describe transitional care; assess, manage, and monitor the transitional needs of burn patients using the Omaha System and refer when applicable; and demonstrate burns rehabilitation competencies (scar, itch, and pain management; psychosocial care; aromatherapy; exercises and splinting; monitoring nutrition and hydration; and infection prevention).	**What (materials and procedures)** • Overview of transitional care • Overview of the Omaha System and its application to clinical practice • Overview of the rehabilitation program • Comprehensive scar management • Rehabilitation therapies/strategies I: (Psychosocial Care- the STEPS Approach, 3-2-1 GO Strategy, and Counseling). • Positive reinforcement • Meditation • Aromatherapy • Rehabilitation therapies/strategies II: (itch management, pain management, and skin/wound care). • Exercises/splinting/positioning • Nutrition-hydration • Infection precautions • Undertaking referrals **When (schedule)** • Training scheduled from 28th August 2020 to 2nd September 2020. • Personal revision schedule **How much (frequency and dose)** • 4.5 h per session (18 h in total) **Who (Provider)** • One professor of rehabilitation • One professor of nursing • One burn care nurse/doctoral student **How (mode of delivery)** • Online via Zoom	Gansu Provincial Hospital	Though the training programme was designed for the group, the facilitators offered assistance to individuals based on questions raised	No modifications made	Entire training schedule was duly adhered to with no deviation

### Intervention

Eligible participants will be randomised to either the treatment or control group. Participants in the control group will continue to utilise optimised usual are comprising of the existing service at the hospital in addition to two social calls by a trained student nurse. Participants in the treatment group will receive the nurse-led transitional burns rehabilitation programme (4Cs-TBuRP) in addition to existing service at the hospital. There are two phases to the 4Cs-TBRP:
Phase 1 (discharge planning/preparation): This phase will take place at least 72 h prior to the day of discharge. Guided by the Omaha System, a comprehensive patient assessment will be performed by the assigned burn care nurse based on a care plan covering environmental, physiological, psychosocial, and health-related behaviour domains will be carried out [35]. The bundle of interventions available is based on the identified need which include environmental (health education to improve sanitation and environmental hygiene within residence), physiological (pain management, itch management, comprehensive scar management, range of motion activities, management of heat sensitivity, skin care, nutritional assessment/support, infection prevention and control measures), psychosocial (social skills training, counselling care, health education, positive reinforcement, spiritual care, meditation, and music therapy), and health-related behaviour (strategies to improve sleep/rest, physical therapy, and participation in activities of daily living). See Table 3 for details regarding the bundle of intervention presented based on the TIDieR checklist.Phase 2 (follow-up phase): This phase comprises of 2 structured WeChat telehealth, 6 structured telephone follow-ups and daytime patient/family-initiated telephone service over an 8-week period. Like the discharge planning phase, care planning and intervention are undertaken using the Omaha System as a guide for the 8-week period. The bundle of interventions available based on the identified need/domain include environmental (health education to improve sanitation and environmental hygiene within residence), physiological (pain management, itch management, comprehensive scar management, range of motion activities, management of heat sensitivity, skin care, nutritional assessment/support, infection prevention and control measures), psychosocial (social skills training, counselling care, health education, positive reinforcement, spiritual care, meditation, music therapy and aromatherapy), and health-related behaviour (strategies to improve sleep/rest, physical therapy, and participation in activities of daily living). Where referrals are required, a referral form will be completed for the service to be provided. Home visits will be carried out if the adult burn survivor has concerns which can best be handled face to face by the nurse (example: assistance with wound care or reinforcing scar management education). See Table 3 for details regarding the bundle of intervention presented based on the TIDieR checklist.

**Table 3 Tab3:** Bundle of intervention

Phase of intervention	TIDieR checklist					
	What (procedures)	Who	How (mode of delivery)	Where (location of the intervention)	When (schedule), and How much (frequency, dose and intensity of interventions)	Tailoring (personalized, titrated or adapted for individual circumstances)
**Discharge planning phase (at least 72 h to discharge)**	Comprehensive patient assessment using the OMAHA System within one week for an adult burn survivor who has a pending discharge status. Interventions will depend on the identified needs and should be classified into teaching, guidance and counselling, treatment and procedures, case management and surveillance. Please ensure to use the intervention scheme for each need. For needs where corresponding schemes are not available, please use the ISBI guidelines.	Nurse case manager (holds a bachelor’s degree or in nursing, and a minimum of 4 years working experience in the Burn Unit)	Face to face and with each patient individually	Burn Unit of the hospital	As needs may change, the first assessment serves as a reference point. The adult burn survivor should be assessed prior to discharge by the nurse case manager.	All components of the intervention scheme may not apply at the same time. Please ensure to match needs at a time to the specific intervention
	Providing support	Nurse case manager	Face to face and with each patient individually	Conducted in the Burn Unit	Once before discharge for 30–45 min (the discussion will be recorded for monitoring and evaluation purposes)	The adult burn survivor is permitted to ask questions beyond the scope of the guidelines; however, the standard components should be covered entirely
**Day of discharge**	Reminder about WeChat Telehealth Service, daytime patient/family-initiated call options and follow-up by the Nurse Case Manager; follow-up on previously identified problems during discharge planning phase	Nurse case manager	Face to face with each patient	Burn Unit	Day of discharge	The assessment is the same, but interventions will vary depending on the goals set with the patient
**Follow-up phase**	Follow-up call for the following: • To confirm home address • Remind the patient/family caregiver of the availability of 24-h hotline service • Follow-up on previously established goals	Nurse case manager	On phone	Home	Phone call 24 h after discharge once (please note for quality and evaluation purposes, the discussion over the phone will be monitored and recorded)	
24 h after discharge						
One-week post-discharge	First structured telephone chat (comprehensive patient assessment should be completed, and interventions instituted where necessary)	Nurse case manager	Via telephone	On phone	Once	Emerging needs may differ, and interventions should be aligned to the needs that are identified
2nd week post-discharge	First WeChat Telehealth follow-up	Nurse case manager	Via WeChat			
3rd week post-discharge	Second structured telephone follow-up	Nurse case manager	On phone	phone	Once	Patients may activate the 24-h service as their needs/concerns evolve (all discussions will be recorded)
4th week post-discharge	Third structured telephone follow-up	Nurse case manager	Phone	phone	Once	Patient’s goals may change or remain same; needs may vary, and interventions should match the identified needs
5th week post-discharge	Fourth structured telephone follow-up	Nurse case manager	On phone	Phone	Once	Patients may activate the 24-h service as their needs/concerns evolve (all discussions will be recorded)
6th week post-discharge	Fifth structured telephone follow-up	Nurse case manager	On phone	Phone	Once	Patients may activate the 24-h service as their needs/concerns evolve (all discussions will be recorded)
7th week post-discharge	Sixth structured telephone follow-up	Nurse case manager	On phone	Phone	Once	Patients may activate the 24-h service as their needs/concerns evolve (all discussions will be recorded)
8th week post-discharge	Second WeChat follow-up	Nurse case manager	Virtual	Virtual	Once	Emerging needs may differ, and care should be aligned to the needs that are identified

### Strategies to improve adherence/fidelity of the intervention

Fidelity will be ensured in this study by using the guidelines offered by Bellg et al. [36] which comprises of (1) ensuring that the intervention dose is the same for all participants across each condition, (2) standardising interventionist training, (3) monitoring the intervention delivery, (4) evaluating participants’ understanding of information provided, and (5) ensuring that participants use the skills taught in the intervention. Adherence reminders will also be given every week to participants during the follow-up via WeChat or telephone. Burn care nurses will document date and length of contacts per participant, referrals to specialists, and performance of intervention components. All calls will be documented, and WeChat messages/images will be reviewed by the team on monthly basis. Also, the care plan sheets for each participant will be reviewed by the research and clinical team via case conferencing held bi-monthly to discuss assessment, management, and evaluation in relation to the study protocol. Nurse case managers will be encouraged to maintain a clinical diary which will be reviewed.

### Study outcomes

#### Primary outcome

*Quality of life*: Quality of life which is defined as the adult burn survivors’ perceptions of their health status and well-being is the primary outcome for the trial and will be assessed at baseline (T0), following completion of the intervention at 8 weeks (T1) and at 4 weeks post-intervention (T2). The outcome will be objectively assessed using the Chinese version of the Burn Specific Health Scale-Brief and EQ-5D-5L. The BSHS is an outcome scale designed specifically for burns patients. It comprises of four areas: physical, psychological, social relations, and general health condition that is consistent with the biopsychosocial model. A recent review has suggested that generic scales are more sensitive than the BSHS-B domains from one-month post-burn [37]. Thus, as the study will cover up to 3 months post-discharge, the BSHS-B and EQ-5D will be used to measure quality of life in the study. The BSHS-B comprises of 40 questions, 9 sub-scales, and 3 domains (physical, mental, and social). Internal consistency of the total instrument has been reported to be *α* = 0.94 with test-retest reliability suggesting that the intraclass correlation coefficient (ICC) ranged from 0.81 to 0.96 with a total score of 0.93 [38]. The Chinese version has 38 items with a reported Cronbach alpha 0.97 and split half reliability of 0.98 [39]. The EQ-5D-5L is a generic tool to assess quality of life. The instrument has five dimensions: mobility, self-care, usual activities, pain/discomfort, and anxiety/depression. Each dimension has 5 levels: no problems, slight problems, moderate problems, severe problems, and extreme problems. The EQ-5D-5L is a valid extension of the 3-level system (EQ-5D-3L) which is found to have improved measurement properties, with reduced ceiling effect, strengthened discriminatory power and established convergent and known-groups validity [40].

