**Fig. 1 Fig1:**
[figure not shown]
Tentative logic model

Developing the intervention proceeded through extensive literature reviews [27–29], exploratory studies, and expert consultations. The current phase seeks to evaluate the effectiveness of the programme in comparison to the existing standard of care. The 4Cs in the intervention represent comprehensiveness, coordination, collaboration, and continuity, which were proven to be essential transitional care elements tested among patients with chronic conditions [30–32]. The 4Cs emphasise on the need for ongoing holistic care required by burn survivors throughout the recovery trajectory. We ask if the nurse-led transitional rehabilitation programme underpinned by multi-disciplinary support can improve quality of life of burn patients, the primary outcome, in the first 12 weeks following discharge. As secondary outcomes, we will investigate the effects on psychological functioning, sleep patterns, itchiness, pain, and physical role functioning. This study protocol was completed in accordance with the SPIRIT 2013 guidelines [33].

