## Trial design

The trial is a double-arm (intervention and control groups), single-centre randomised controlled trial with 1:1 allocation ratio and a follow-up process evaluation phase. We will firstly undertake a pilot feasibility phase and follow-up with the full-scale trial. The null hypothesis is that there will be no difference regarding outcomes between the intervention and control groups. The alternative hypothesis is that there will be statistically significant differences between the participants undergoing the nurse-led programme of care and participants receiving the existing standard of care.

The follow-up process evaluation phase will employ a multi-method approach (qualitative and quantitative strands) to examine the process and issues during the implementation process [34]. Twelve process measures covering domains such as recruitment, follow-up, intervention delivery, and data collection will be considered in the process evaluation phase (see Table 1). The qualitative strand will capture changes in the implementation process and experiences with the intervention from the perspectives of adult burn survivors and nurse case managers. The quantitative strand will offer insight into key process variables such as recruitment, follow-up, and adherence rates. Details regarding the process evaluation phase (process measures, variables, methods, and participants) are provided in Table 1.

**Table 1 Tab1:** Outline of process evaluation for the nurse-led transitional rehabilitation program

Process measures	Process variables	Method	Participants and data collection method
Recruitment and selection rate	• Number of burn survivors screened at the study setting. • Number of participants from the sample of eligible persons. • Number of participants versus aimed number	Enrolment record review	Site manager (research team member)/data collection team
Barriers and facilitators in recruitment and selection process	• Motivation of participating eligible persons. • Experience with recruitment and selection	Semi-structured interviews	Adult burn survivors Recruiting nurses
Follow-up and attrition rate	• Number of participants completing follow-up	Follow-up record review	Site manager (research team member)/data collection team
Barriers and facilitators for follow-up	• Reasons for drop-out • Motivation for continued participation	Semi-structured interviews	Adult burn survivors

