### Sampling and sample size estimation

Subjects will include adult burn survivors with burn size ≥ 10% TBSA from the Burn Unit. Upon recruitment, randomisation to either control or treatment group (ratio 1:1) with a blinded approach will be carried out. For the pilot phase of the project, the pilot feasibility sample size rule suggested by Whitehead, Julius, Cooper, & Campbell will be used [50]. The rule specifies that a total sample size of 25 participants per arm. Considering possible attrition rate of 20% that has been reported in burn care literature implies that an additional 5 participants will be added to both arms summing up to 30 participants per arm (total = 60 participants).

For the main trial, the sample size calculation based on the primary outcome measure (Burn Specific Health Scale) at 95% confidence level, 90% statistical power and moderate effect size will yield a total of 38 participants per arm [51–53]. Considering an attrition rate of 20%, the final sample size will be 45 participants per arm (total = 90 participants). In all, 150 participants will be recruited for the entire study. For the follow-up process evaluation phase, we will conveniently recruit up to fifteen [15] participants from each arm whilst being guided by the principle of data saturation in addition to the burn care nurses delivering the intervention to complete the qualitative strand. Data saturation will be determined at the point where no new data emerges. The quantitative strand will include review of the recruitment, enrolment, and follow-up records.

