### Statistical methods and analysis

The data analysis plan will proceed through data entry and cleaning, missing data management and statistical analysis. All quantitative data will be coded and entered to SPSS Version 25 (SPSS, an IBM company, Chicago, Illinois, USA). The data will be inspected visually with random searches and frequency counts to ascertain its completeness. Demographic and clinical characteristics will be compared using chi-square test (for normally distributed data) or Mann-Whitney *U* test (data that is not normally distributed). Between group differences will be assessed using independent t test (for continuous data). Both per-protocol (PP) and intention to treat analysis (ITT) will be performed respectively on participants who completed the entire intervention and those recruited to participate. Methods for longitudinal data such as generalised estimating equations (GEE) will be employed. All statistical tests will be conducted at 95% confidence interval.

Qualitative data emerging from the follow-up process evaluation phase will be analysed using content analysis [54]. All audio recordings will be transcribed verbatim and translated from Chinese to English using the Trint Automation Software. The transcripts will be inspected for correctness and completeness by two native speakers who are also fluent in English. The final versions will be exported to the NVivo version 10 software for data management and analysis by two researchers with ongoing consultation with the research team. The analytical process will commence with reading all data repeatedly to achieve immersion and obtain a sense of the whole. Then, data will be read line by line to formulate codes by first highlighting the exact words from the text that appear to capture key thoughts. Following this, the researcher will approach each transcript by making notes of initial impressions. Following the formulation of the codes, labels for the code will be formulated directly from the text. At this point, an initial coding scheme will be formulated. Similar codes will be sorted to formulated categories. Emergent categories will be used to organize and group codes into clusters [54].

Data emerging from the quantitative strand will collated into SPSS Version 25. We will employ descriptive statistics to ascertain the distribution of the data.

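### The protocol contradicts itself on the primary quality-of-life measure (two scales in one section, one in another) and names no primary time or contrast, so the error rate of the primary claim is not held at 5%

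*Protocol article*

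**What the plan says.** The statements that bear on the primary claim sit in five sections of the protocol article.

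- **Primary outcome, instruments.** Quality of life is the primary outcome: "The outcome will be objectively assessed using the Chinese version of the Burn Specific Health Scale-Brief and EQ-5D-5L". The same paragraph repeats that "the BSHS-B and EQ-5D will be used to measure quality of life in the study". Neither scale is ranked above the other.
- **Primary outcome, times.** After baseline, assessment is "following completion of the intervention at 8 weeks (T1) and at 4 weeks post-intervention (T2"). Neither time is called primary.
- **Sampling and sample size estimation.** The main trial is sized by "the sample size calculation based on the primary outcome measure (Burn Specific Health Scale"). Only one scale is named here.
- **Background and rationale.** The research question is whether the programme "can improve quality of life of burn patients, the primary outcome, in the first 12 weeks following discharge". That window contains both T1 and T2.
- **Trial design.** "The null hypothesis is that there will be no difference regarding outcomes between the intervention and control groups". The null is not tied to a scale, a time or a contrast.
- **Statistical methods and analysis.** "All statistical tests will be conducted at 95% confidence interval". Group differences are to be tested by independent t test, and longitudinal methods, with GEE given as an example, are also to be used. No contrast is named for either.

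**The concern.** Two sections disagree on what the primary measure is, and no section says at which time, or by which contrast, the primary question is decided. With every test at the same level and no stated rule for success, the primary claim could rest on any of several results, and the choice could be made after the data are seen.

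Two things are at stake. First, the false-positive rate of the primary claim is above 5% under any reading that lets more than one result count. Second, if the burn scale and EQ-5D-5L, or T1 and T2, give different answers, the protocol does not settle which answer is the trial's result. For the scales it gives two conflicting pointers; for the times it gives none.

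**Working it through.** **What the plan's own figures cover.** The protocol states no error rate for the primary claim, so there is none to reproduce. Its related figure is 38 per arm, from 95% confidence, 90% power and a moderate effect with no number attached. For one two-sided 5% test, n per arm = 2(1.960 + 1.282)² / d². At d = 0.75 this is 2 × 10.51 / 0.5625 = 37.4, so 38. At the conventional d = 0.5 it is 84.1, so 85. The size of the assumed effect is a separate matter. What counts here is that 38 is consistent with one test at 5% and contains no allowance for more.

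**Inputs for the error rate.**

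- Scales under the primary outcome: 2 (Primary outcome) or 1 (Sampling and sample size estimation).
- Post-baseline times: 2 (Primary outcome).
- Level per test: 0.05 (Statistical methods and analysis). It is taken as two-sided because the alternative hypothesis in Trial design has no direction.
- Correlations between scales and between times: not given in the document. They are assumed, and a range is shown.

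**Independent tests.**

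- Four results: 1 − 0.95⁴ = 0.185.
- Two results: 1 − 0.95² = 0.0975.

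**Correlated tests.** Four standard normal test statistics were simulated under the null (1,000,000 draws). The correlation was r(scale) between scales at the same time, r(time) between times on the same scale, and their product otherwise. A false positive is any |Z| above 1.96 among the results that count.

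| r(scale) / r(time), assumed | Either scale, either time (4 results) | Burn scale only, T1 or T2 (2 results) |
|---|---|---|
| 0 / 0 (exact) | 18.5% | 9.75% |
| 0.5 / 0.5 | 16.2% | 9.1% |
| 0.7 / 0.7 | 13.6% | 8.3% |
| 0.8 / 0.8 | 12.0% | 7.8% |
| 0.9 / 0.9 | 9.8% | 7.1% |

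**One joint test per scale.** If GEE gave one test across times for each scale and either scale could carry the claim, two results would again count. The rate would be about 7% to 9% at between-scale correlations of 0.9 to 0.5.

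**One scale, one contrast.** The rate is 5%.

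**Splitting the level instead.** Bonferroni over four results uses 0.0125 each. At 38 per arm and d = 0.75, power per test falls from 90.5% to 78.0%. Keeping 90% power would need 51 per arm before dropout. Naming one contrast avoids that loss.

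**The case against.** The strongest case against the point has four parts.

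*No rule says that any one result wins.* This is right. A reader might infer that the plan gives the trial four chances to succeed, each at 5%. The document does not say so: listing two tools and two visits is not a decision rule. The four-result figures describe what the text leaves open, not what it prescribes.

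*The sample-size section settles the scale.* It does point to the burn scale, and on that reading EQ-5D-5L cannot carry the claim and at most two results count. But the Primary outcome section says otherwise, and the two must be reconciled. T1 and T2 remain unranked either way.

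*GEE could give a single test across times.* It could. But the method is offered as an example, its contrast is not named, and t tests are specified as well. It reduces the possible count without fixing it.

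*Multiplicity belongs in an analysis plan that is not shown.* Adjustment methods and the exact model may well sit there, and their absence is not raised. Which scale and which time are primary is protocol content, and here the article contradicts itself on the scale.

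Two further inferences should be avoided. The secondary scales do not belong in the error rate of the primary claim, because the Objectives section separates them from quality of life. And the remark that generic scales may be more sensitive from one month after the burn is the stated reason for using both tools. It is not a prediction that they will disagree.

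**Conclusion.** The point holds in this form: the protocol gives two unranked primary scales in one section and one in another, names no primary time or contrast, and tests everything at 5%. The error rate of the primary claim is therefore not fixed at 5%.

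Its size depends on the reading. It is about 7% to 9% if only the burn scale counts at two times (9.75% if independent), and about 10% to 16% if either scale at either time counts (18.5% if independent). The ranges rest on assumed correlations of 0.9 to 0.5 and on two-sided tests. The count of four is an upper reading of what the wording allows, not a stated success rule.

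**What to change.** 1. In Primary outcome, name the BSHS-B total score as the single primary measure, which agrees with the sample-size section, and move EQ-5D-5L to the secondary outcomes.
2. Pre-name one primary between-arm contrast, tested at two-sided 5%. This can be the difference at one stated time or one joint GEE test over T1 and T2. The choice is the investigators', and it should match the 12-week question in Background and rationale.
3. Make the remaining time or contrast secondary.
4. Reword the null hypothesis in Trial design to that one contrast.

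The cost is protocol wording. No new data or visits are needed, and the number of participants need not change on this account. The real concession is that EQ-5D-5L, or the time or contrast not chosen, can no longer carry the primary claim. Separately, and as a minor wording point, the description of the assessment as objective should go, since the outcome is defined by participants' own perceptions and participants are not blinded.
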